## Abstract

**Background:** Pulmonary complications are common in patients after upper abdominal surgery, resulting in poor clinical outcomes and increased costs of hospitalization. Enhanced Recovery After Surgery Guidelines strongly recommend early mobilization post-operatively; however, the quality of the evidence is poor, and indicators for quantifying the effectiveness of early mobilization are lacking. This study will evaluate the effectiveness of early mobilization in patients undergoing an upper abdominal surgery using electrical impedance tomography (EIT). Specifically, we will use EIT to assess and compare the lung ventilation distribution among various regions of interest (ROI) before and after mobilization in this patient population. Additionally, we will assess the temporal differences in the distribution of ventilation in various ROI during mobilization in an effort to develop personalized activity programs for this patient population.

**Methods:** In this prospective, single-center cohort study, we aim to recruit 50 patients after upper abdominal surgery between July 1, 2021 and June 30, 2022. This study will use EIT to quantify the ventilation distribution among different ROI. On post-operative day 1, the nurses will assist the patient to sit on the chair beside the bed. Patient's heart rate, blood pressure, oxygen saturation, respiratory rate, and ROI 1-4 will be recorded before the mobilization as baseline. These data will be recorded again at 15, 30, 60, 90, and 120 min after mobilization, and the changes in vital signs and ROI 1-4 values at each time point before and after mobilization will be compared.

**Ethics and Dissemination:** The study protocol has been approved by the Institutional Review Board of Liaocheng Cardiac Hospital (2020036). The trial is registered at chictr.org.cn with identifier ChiCTR2100042877, registered on January 31, 2021. The results of the study will be presented at relevant national and international conferences and submitted to international peer-reviewed journals. There are no plans to communicate results specifically to participants. Important protocol modifications, such as changes to eligibility criteria, outcomes, or analyses, will be communicated to all relevant parties (including investigators, Institutional Review Board, trial participants, trial registries, journals, and regulators) as needed via email or in-person communication.

## Background

Post-operative pulmonary complications (PPCs), such as pneumonia, severe atelectasis, and respiratory failure, occur in about 10–50% of patients after a major upper abdominal surgery (1–3). Several factors contribute to the development of PPCs, including post-operative pathophysiological reductions in lung volumes, respiratory muscle function, mucociliary clearance, and pain inhibition of respiratory muscles (4). Following an upper abdominal surgery, PPCs are significantly associated with poor patient outcomes and result in an increased likelihood of rehospitalization, increased mortality and morbidity, longer hospital length of stay, and higher costs (5–10). Enhanced Recovery After Surgery (ERAS) Society Guidelines recommend early mobilization to improve recovery, reduce complication rates, and shorten inpatient hospital stays by reducing the physiologic derangement and stress response after surgery (11–14). While few studies have explored the method and duration for implementing mobilization, the indicators for measuring the effectiveness of post-operative early mobilization on pulmonary outcomes are lacking.

Electrical impedance tomography (EIT) is a non-invasive, radiation-free, bedside monitoring technique that provides dynamic images based on changes in the electrical conductivity of body sections through digital reconstruction (15). Within the chest, impedance can vary dynamically due to changes in lung volume (such as during respiration) and/or due to changes in blood and fluid content (such as within the heart during the cardiac cycle) (16). Thus, EIT can help evaluate the patient's ventilation distribution, which could lead to adjustments to the patient's early mobilization method and duration.

This study aims to evaluate the effect of post-operative early mobilization on lung ventilation function using EIT by assessing the ventilation distribution among various regions of interest (ROI) before and after mobilization in patients undergoing upper abdominal surgery. Additionally, the temporal differences in the distribution of ventilation in various regions of interest during mobilization will be explored to provide a theoretical basis for the development of personalized mobilization plans and precise treatment for patients after upper abdominal surgery.

## Methods and Analysis

### Study Design

This prospective, single-center, single-cohort study will be conducted in the Surgical Intensive Care Unit (SICU) at the Liaocheng Cardiac Hospital in Shandong Province in China.

### Participant Characteristics

Inclusion criteria will consist of the following: patients ≥18 years old admitted to the SICU after undergoing a laparoscopic upper abdominal surgery, such as gastrectomy, pancreaticoduodenectomy, hepatectomy, or esophagectomy, with a written informed consent by the patient or their legally authorized representative. Patients will be excluded for the following reasons: severe pain (11-point numerical rating scale [NRS] ≥7), agitation, ongoing need for ventilation, major hemodynamic instability, cardiorespiratory failure, absence of consent, and technical limitations for EIT monitoring [for example, cardiac electric device, morbid obesity (body mass index [BMI]>30kg/m^2^), or chest bandages (17)]. Patients will also be excluded if mobilization is deemed unsafe for other reasons. Once the patient's eligibility is confirmed, a clinical coordinator will describe each relevant aspect of the study to the patient and obtain a written informed consent from the patient or their legally authorized representative.

### Electrical Impedance Tomography Technique and Measurements

EIT allows calculation of regional ventilation distribution by assessing change in relative impedance in one predefined cross-sectional slice of the lung. EIT monitoring will be performed using the PulmoVista 500 (Dräger Medical, Lübeck, Germany). A thoracic belt with 16 electrodes will be placed at the fourth intercostal space, such that the 1st electrode will be at the left bound of the sternum and the 16th electrode at the right sternum (Figure 1). EIT images are divided into four equidistant “regions of interest” (ROI) from ventral to dorsal (Figure 2). ROI 1-2 represents the ventral region, namely the non-gravity dependent region. ROI 3 to 4 represents the dorsal region, or gravity-dependent region. Moisture ratio of ROI 1 to 4 can be displayed on the monitor. The electrodes will always be placed in the same mode and kept in place during the entire measurement protocol. Participants will be asked to not speak and to limit trunk movements during the recording period.

**Figure 1 F1:**
[figure not shown]
Location of the EIT bind. EIT, electrical impedance tomography.

**Figure 2 F2:**
[figure not shown]
EIT image partition diagram. ROI 1, ROI 2, ROI 3, and ROI 4 were, respectively, from top to bottom. From left to right, right lung and left lung. ROI, region of interest; EIT, electrical impedance tomography.

### Procedure

Study procedures will be carried out in the following steps:

Once a patient meets inclusion criteria and provides a written informed consent, the following data will be collected: age, sex, weight, height, BMI, smoking history, type and duration of surgery, comorbidities, arterial blood gas analysis (PH, PaO_2_, PaCO_2_, FiO_2_), chest X-ray or computed tomography (CT), pain (11-point NRS), and the time from admission to the ICU to the first mobilization.The following baseline parameters will be recorded when the patient is in decubitus position (T_0_): heart rate (HR), blood pressure (BP), oxygen saturation (SO_2_), respiratory rate (RR), and EIT ROI 1-4. The duration of each EIT recording will be 2 min.The patient will be seated in a chair beside the bed with assistance. Oxygen therapy method and oxygen concentration will be the same as that before getting out of bed.The parameters presented in step 2 will be recorded at 15 min (T_1_), 30 min (T_2_), 60 min (T_3_), 90 min (T_4_), and 120 min (T_5_) for each patient after getting out of the bed.

After patients reach the 120-min time point, their participation in the study will be complete. No further interaction with the enrolled patients is planned.

### Outcome Measures

The primary outcomes include the improvement in homogeneity of pulmonary ventilation distribution after mobilization and optimal duration of early mobilization. Secondary outcomes include optimal duration of early mobilization for different surgical methods; correlation between bed rest time and optimal duration of early mobilization; and correlation between blood oxygen saturation, oxygenation index, and improvement in homogeneity of pulmonary ventilation distribution.

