### Definitions

Homogeneity index is defined as the ratio of EIT values of ventral to those of dorsal ROIs; thus, lower levels (~1.0) represent better homogeneity of ventilation (18).Optimal duration of early mobilization is defined as the mobilization time at which homogeneity index is closest to 1.Bed rest time is the time from the start of surgery to the time of first mobilization.

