### Statistical Analysis

A prior study that used EIT to assess ventilation distribution in patients undergoing major open abdominal surgery found that a two-sided significance level (α) of 0.05 and a target power of 80% would require 10 subjects (19). We aim to recruit 50 patients, surpassing the minimum necessary for our target power and significance level. Analyses will be conducted using SPSS 21.0 (IBM, Armonk, New York, USA). Continuous variables will be expressed as means (95% confidence intervals, CI) or as medians (interquartile range). Categorical variables will be analyzed using the chi-square test. Means or medians will be compared between groups using the *t*-test, the Mann-Whitney *U*-test, and one-way analysis of variance with F- or Kruskall-Wallis tests, when appropriate. Pearson correlation or Spearman rank correlation coefficient will be used to assess the correlation between variables, as appropriate. Intention-to-treat analyses will be carried out using mixed models. All tests will be 2-sided, and significance will be set at the 0.05 probability level.

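### The primary improvement in homogeneity has no designated time point or contrast; testing the index against T0 at each of five times at 0.05 would give roughly a 9–19% chance of a significant result with no true change

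*Protocol article*

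**What the plan says.** Protocol article, Outcome Measures, names two primary outcomes: "The primary outcomes include the improvement in homogeneity of pulmonary ventilation distribution after mobilization and optimal duration of early mobilization". Nothing there says at which time, or by which contrast, improvement is to be judged.

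The Definitions section supplies the measure: "Homogeneity index is defined as the ratio of EIT values of ventral to those of dorsal ROIs", with values near 1.0 taken as better. It defines the second primary outcome as a selected time: "Optimal duration of early mobilization is defined as the mobilization time at which homogeneity index is closest to 1".

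The Procedure section sets one baseline recording (T0, lying) and five recordings in the chair (T1 to T5), at 15 to 120 min. On what is to be done with these recordings, the Abstract says that "the changes in vital signs and ROI 1-4 values at each time point before and after mobilization will be compared".

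The Statistical Analysis section lists several tests and adds "Intention-to-treat analyses will be carried out using mixed models". It closes with a rule for all of them, which fixes one level and sidedness throughout: "All tests will be 2-sided, and significance will be set at the 0.05 probability level". It does not say which test, contrast or time point is primary.

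**The concern.** The time frame of a primary outcome is part of its definition, and here it is left open in the section that defines the outcome. With five post-baseline recordings and one significance level for every test, a reader following the text could claim improvement from any one of five comparisons. Two things are then at stake:

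- The error rate for the first primary conclusion would not be the stated 5%.
- The change reported would tend to be the largest of five, and so overstated.

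This matters because the Strengths and Limitations section presents the study as designed to demonstrate that early mobilization improves ventilation distribution. That is a confirmatory aim.

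**Working it through.** **Inputs from the protocol article**
- Planned sample size: 50 (Statistical Analysis).
- Post-baseline times: 5, at 15, 30, 60, 90 and 120 min (Abstract, Procedure).
- Significance level: two-sided 0.05 for every test (Statistical Analysis).

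**Inputs assumed**
- The index is tested against T0 at each time with a paired test. The article does not state this.
- The correlation between the five contrasts is not given, so a range is used.

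**The plan's own figures.** A single paired t-test at one pre-named time, simulated with n = 50 and no true change, was significant in 4.8% to 5.2% of trials. The stated 0.05 is therefore right for one test. The stated requirement of 10 subjects cannot be rebuilt, because no effect size, SD or test is given. If it refers to one paired t-test at two-sided 0.05 with 80% power, it implies a change of about 1.00 SD of the within-patient difference.

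**Upper reference, five independent tests.** 1 − (1 − 0.05)^5 = 1 − 0.774 = 0.226. This is too high here because all five contrasts share T0.

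**Effect of the shared baseline.** Suppose all six recordings have variance σ² and common correlation ρ. Then:
- Cov(Tj − T0, Tk − T0) = ρσ² − ρσ² − ρσ² + σ² = (1 − ρ)σ²
- Var(Tj − T0) = 2(1 − ρ)σ²
- Correlation between contrasts = (1 − ρ)σ² / [2(1 − ρ)σ²] = 0.5, whatever ρ is.

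Varying ρ under this structure therefore repeats one scenario. Simulation (n = 50, 40,000 null trials per setting) gives 18.2% to 18.7% for ρ from 0 to 0.9. With correlation decaying exponentially over time (time constants 15 to 240 min) the figure is 16.2% to 18.2%.

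**Higher contrast correlation.** T0 is recorded lying and T1 to T5 seated. If patients differ in their response to posture, the contrasts will correlate more strongly than 0.5. Simulated at n = 50 with no true change:

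| Correlation between contrasts | At least one of five significant | At least one false improvement (nominal 2.5%) |
|---|---|---|
| 0.5 | about 18% | about 9% |
| 0.7 | about 15% | about 7.5% |
| 0.9 | about 10% | about 5% |
| 0.95 | about 8.5% | about 4.3% |

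Relative to nominal this runs from 8.5/5 = 1.7 to 18/5 = 3.6.

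**After the fix.** One named contrast or one global test keeps the primary test at 5%. For the individual times, the strictest Holm step over five contrasts is 0.05/5 = 0.01. For a paired t-test with n = 50 and 80% power, the detectable change is 0.40 SD at 0.05 and 0.50 SD at 0.01. Both are well below 1.00 SD.

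**The case against.** **Five tests of the index are not stated.** The Abstract sentence covers vital signs and ROI 1–4 values, not the index, and the Statistical Analysis section names no paired test. It does name mixed models, which could supply one test of time. This stands, and it is why the size is given conditionally. It does not remove the point, because no such test is made primary. The step to the index is also short, since the index is a ratio of those same ROI values.

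**Multiplicity control may sit in an unseen analysis plan.** A missing adjustment alone would be no finding. The open time frame of the primary outcome and the flat 0.05 are, however, what this document itself fixes.

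**The two-sided rate overstates the problem.** About half of the 9–19% is significant worsening. This is right, so the rate for false improvement is given as well. It still exceeds its nominal 2.5% in every setting tried.

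**Stronger readings the document does not support.**
- A reader might infer that the second primary outcome is also tested at 0.05 and adds to the error. It is a selected time with no null hypothesis and no stated test, so it adds no computable alpha.
- A reader might count four ROIs at five times as 20 chances for a positive primary result. Homogeneity is defined by the ventral-to-dorsal ratio, so a change in one ROI is not the primary outcome.
- A reader might take 18–19% as the settled figure. It is the upper part of a range that depends on assumed correlations.

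**Conclusion.** The point holds in limited form. The first primary outcome has no designated time point or contrast, five post-baseline recordings are available, and every test is set at two-sided 0.05. If the index is tested against T0 at each time, the chance of at least one significant result with no true change is about 9–19%, or roughly 1.7 to 3.6 times nominal. For a false improvement it is about 4–9% against 2.5%. These figures assume 50 patients with complete data, paired tests, and contrast correlations from 0.5 to 0.95, none of which the article supplies apart from the planned 50. That the primary contrast is unnamed needs no assumption. This should be corrected, and the Study Status section places the study before recruitment, so it can be settled before data are seen.

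**What to change.** Name one primary test for the homogeneity index, at two-sided 0.05, within the mixed model already planned. Either form will do:

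- one pre-specified contrast with T0, at a named time or for the mean of T1 to T5; or
- one global test of time.

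A global test has no direction, so if it is chosen, state that the direction is read from the estimated changes. Test the individual times against T0 only if the primary test is significant, with Holm adjustment. Report the ROI 1–4 and vital-sign comparisons as exploratory.

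**Cost.** No extra patients or measurements are needed. The individual time contrasts lose some power, with a detectable change of 0.50 SD instead of 0.40 SD at the strictest Holm step. The mean of T1 to T5 speaks less directly to the question of duration than a named time does, so the choice should follow the study's main question. The Ethics and Dissemination section treats changes to outcomes or analyses as important modifications, so this one must be communicated to the review board, the registry and the other parties listed there.

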### Definitions

Homogeneity index is defined as the ratio of EIT values of ventral to those of dorsal ROIs; thus, lower levels (~1.0) represent better homogeneity of ventilation (18).Optimal duration of early mobilization is defined as the mobilization time at which homogeneity index is closest to 1.Bed rest time is the time from the start of surgery to the time of first mobilization.

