EIT assesses gas distribution in the lungs by monitoring the changes in thoracic impedance caused by intrapulmonary ventilation; gas distribution thus measured by EIT correlates well with that measured by CT (34–36). In the upright sitting position, the diaphragm is lowered due to the action of gravity, and the area for lung movement is enlarged. This significantly increases the number of alveoli that are effectively involved in breathing, making the distribution of air in the lungs more uniform. Bed rest induces heterogeneity of ventilation, especially in the dorsal regions (37), which can be prevented by modifying positive end-expiratory pressure (PEEP) levels with position changes (38). In this study, the objective is to demonstrate that patient mobilization induces ventilation redistribution without changes in PEEP.

EIT images possess a high temporal and functional resolution, allowing the visualization of dynamic physiological and pathological changes on a breath-by-breath basis. The use of EIT in clinical practice is supported by several studies demonstrating a good correlation between impedance tomography data and other validated methods of measuring lung volume, such as PEEP titration, lung retraction, quantification of pulmonary edema, assessment of mode of ventilation, regional distribution of ventilation, and effects of position changes (39, 40).

Changes in body position are known to influence respiratory mechanics and the pulmonary gas exchange; however, mechanisms involved in the lung aeration and oxygenation improvements are not clear. Nevertheless, we hypothesize that an effective redistribution of air volume induced by the trunk's upright position could prevent respiratory monotony in the resting state and also improve the air volume redistribution (41). Other possible mechanisms include enhanced diaphragm utilization and an increase in transpulmonary pressure. Moreover, because increased tidal impedance variation was observed in the posterior lung regions during active exercise without PaCO_2_ changes, we suggest that oxygenation improvement is not explained by marked increases in minute ventilation. Sitting, standing, and walking increases heart rate and systolic and diastolic blood pressure (42). The active use of a cycle ergometer for 5 min by subjects in the ICU caused a slight increase in the sensation of dyspnea, from mild to moderate and was associated with increases in heart and breathing frequency (43).

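### The ventral/dorsal homogeneity index is given two directions of benefit that conflict below 1, and plain distance from 1 scores mirror-image imbalances unequally

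*Protocol article*

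**What the plan says.** Under Electrical Impedance Tomography Technique and Measurements, the protocol article divides the image into four regions and groups them in pairs: "ROI 1-2 represents the ventral region, namely the non-gravity dependent region" and "ROI 3 to 4 represents the dorsal region, or gravity-dependent region". Definitions builds the index from these pairs and gives it a direction: "Homogeneity index is defined as the ratio of EIT values of ventral to those of dorsal ROIs; thus, lower levels (~1.0) represent better homogeneity". The sentence after it applies a different criterion: "Optimal duration of early mobilization is defined as the mobilization time at which homogeneity index is closest to 1".

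Under Outcome Measures, "The primary outcomes include the improvement in homogeneity of pulmonary ventilation distribution after mobilization and optimal duration of early mobilization". The secondary outcomes build on the same two quantities, for example the "correlation between blood oxygen saturation, oxygenation index, and improvement in homogeneity of pulmonary ventilation distribution".

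The article sets no floor at 1, names no scale on which closeness to 1 is measured, and gives no other numerical definition of improvement. The phrase about lower levels is therefore the only direction stated for the first primary outcome.

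**The concern.** A ventral/dorsal ratio equals 1 at balance and falls below 1 as soon as ROI 3-4 receive more than ROI 1-2. Below that point the two sentences in Definitions give opposite verdicts on the same change. One primary outcome could record an improvement where the rule behind the other records a worsening.

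The second sentence has its own difficulty. The plain reading of closest to 1 is the smallest absolute difference between the ratio and 1. A ratio runs from 0 to 1 on one side of balance and from 1 upwards without limit on the other. The same imbalance therefore costs less when it is dorsal-heavy than when it is ventral-heavy, and the choice of optimal time can lean towards overshoot.

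**Working it through.** **Inputs.** The index is r = V/D, with V the ventral value (ROI 1-2) and D the dorsal value (ROI 3-4), from Definitions and the EIT measurement section. The article gives no ventral or dorsal values, so every split below is illustrative. I take V + D = 100%, so the ventral share is r/(1 + r). There is no figure in the plan to reproduce beyond its anchor: 50:50 gives r = 1.0, as stated.

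**Step 1: the two rules below 1.** Take a patient who moves from 52:48 to 40:60.
- r goes from 52/48 = 1.083 to 40/60 = 0.667, a fall of 0.417. Under lower is better, this is an improvement.
- |r - 1| goes from 0.083 to 0.333. Under closest to 1, it is a worsening.

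If every value stays at or above 1, lower and closer to 1 are the same thing and the rules order time points identically.

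**Step 2: mirror images on plain distance.**

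| Split | r | distance from 1 | Mirror | r | distance from 1 | Ratio of distances |
|---|---|---|---|---|---|---|
| 55:45 | 1.222 | 0.222 | 45:55 | 0.818 | 0.182 | 1.22 |
| 60:40 | 1.500 | 0.500 | 40:60 | 0.667 | 0.333 | 1.50 |
| 70:30 | 2.333 | 1.333 | 30:70 | 0.429 | 0.571 | 2.33 |

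On |ln r| each pair ties: 0.201, 0.405 and 0.847.

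**Step 3: can closest to 1 pick the worse time?** Compare 58:42 with 40:60 in one patient.
- Plain distance: |1.381 - 1| = 0.381 against |0.667 - 1| = 0.333, so 40:60 is chosen.
- Distance of the ventral share from 50%: 8 points against 10 points, so 40:60 is the less balanced.
- |ln r|: 0.323 against 0.405, the same conclusion.

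**Step 4: how wide is the error?** If all of a patient's values lie on one side of 1, plain and log distance rank them identically. Now take one value r > 1 and another s < 1. Plain distance prefers s when s > 2 - r; log distance prefers s when s > 1/r. They disagree for s between 2 - r and 1/r, a window of width 1/r - (2 - r) = (r - 1)²/r. The worst case is s just above 2 - r. The last column is the extra imbalance accepted there: [50% - (2 - r)/(3 - r)] - [r/(1 + r) - 50%].

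| r | Window for s | Width | Worst-case extra imbalance (points of share) |
|---|---|---|---|
| 1.1 | 0.900 to 0.909 | 0.009 | 2.63 - 2.38 = 0.25 |
| 1.2 | 0.800 to 0.833 | 0.033 | 5.56 - 4.55 = 1.01 |
| 1.3 | 0.700 to 0.769 | 0.069 | 8.82 - 6.52 = 2.30 |
| 1.5 | 0.500 to 0.667 | 0.167 | 16.67 - 10.00 = 6.67 |

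The error always favours the dorsal-heavy time.

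**The case against.** The parenthesis (~1.0) names the target, and the following sentence repeats it. Read together, the authors plainly expected the index to fall towards 1 from above. The Discussion fits this: it says that bed rest disturbs ventilation mainly in the dorsal regions, so a dorsal gain would first move the ratio towards 1. A large overshoot, such as 1.25 to 0.60, is already scored as worse by the optimal-duration rule (distance 0.25 to 0.40). All of this stands, and it limits the size of the problem. It does not remove the conflict, because nothing stops the ratio at 1 and improvement has no other stated direction.

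Four stronger readings are tempting, and the article does not support them.
- A reader might infer that a fall in the mean index will be reported as improvement, with patients above and below 1 cancelling. Statistical Analysis speaks of comparing means or medians in general, but nowhere says that the raw index is averaged in this way. The secondary outcome relating time in bed to optimal duration needs an optimal time for each patient, so no cancelling arises there.
- A reader might take the Discussion's remark that "increased tidal impedance variation was observed in the posterior lung regions during active exercise" as evidence of overshoot. It concerns exercise, while patients here sit in a chair, and it does not say that ventilation became dorsal-dominant.
- A reader might say that the index fails because it ignores distribution within each half. The Abstract already plans comparison of ROI 1-4 at each time point, so this is not part of the point.
- A reader might conclude that optimal times will be biased towards overshoot. Without ventral and dorsal values that is a possibility, not a demonstrated effect.

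**Conclusion.** The point holds in a limited form. Definitions gives the index two directions that agree only at or above 1, and the conflict reaches both primary outcomes and the secondary outcomes derived from them. Separately, plain distance from 1 can select the more unbalanced time, but only when a patient's values lie on both sides of 1 and within the window shown above. That window is negligible near balance and material only for larger imbalances.

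This rests on reading closest to 1 as an absolute difference on the ratio scale, which is the plain meaning but is not spelled out, and on the index falling below 1 in some patients, whose frequency the article does not give. It is a correctable defect in the definition of the primary variable. It does not show that the study's results would be wrong.

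**What to change.** In Definitions, remove the statement that lower levels are better. Define improvement for each patient as a decrease from T0 in one prespecified symmetric distance from balance, either |ln(V/D)| or |ventral share - 50%|. The two rank recordings identically but have different means and would give different tests, so one must be chosen in advance. Compute it per patient and time before any averaging, and use the same distance to determine the optimal duration. Report the signed log ratio, ln(V/D), alongside so that overshoot is visible.

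The change needs no new measurements, since ROI 1-4 are recorded at T0 to T5. Study Status describes recruitment as still in preparation, so the choice could be made before any results are seen. There is a price: an absolute distance is folded at zero, so it is skewed and is inflated by measurement noise near balance, and the scale is less familiar to clinical readers than the raw ratio.

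### The optimal-duration rule leaves out the pre-mobilization reading, so a patient or cohort less homogeneous at every seated time than in bed is still assigned an optimum of 15 to 120 min

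*Protocol article*

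**What the plan says.** Outcome Measures makes the duration a primary outcome: "The primary outcomes include the improvement in homogeneity of pulmonary ventilation distribution after mobilization and optimal duration of early mobilization". The same variable returns in two secondary outcomes, one by surgical method and one described as "correlation between bed rest time and optimal duration of early mobilization".

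Definitions gives the scale, "Homogeneity index is defined as the ratio of EIT values of ventral to those of dorsal ROIs", with values near 1 taken as better, and then the rule: "Optimal duration of early mobilization is defined as the mobilization time at which homogeneity index is closest to 1".

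Procedure separates the bed reading from the seated readings. For the first it says "The following baseline parameters will be recorded when the patient is in decubitus position (T_0", and this comes before the patient is moved to the chair. The same parameters "will be recorded at 15 min (T_1_), 30 min (T_2_), 60 min (T_3_), 90 min (T_4_), and 120 min (T_5_) for each patient" once the patient is out of bed.

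The Abstract adds that "the changes in vital signs and ROI 1-4 values at each time point before and after mobilization will be compared". That comparison does use the bed reading, but nothing ties it to the choice of the optimal time.

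**The concern.** T0 is labelled a baseline and is taken before the patient is seated, so on the ordinary reading it is not a mobilization time and cannot be selected. The rule therefore chooses only among the five seated readings. It sets no condition that the chosen reading be better than the bed reading, and it has no category for a patient in whom none is.

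The label *optimal duration* suggests a time at which mobilization did some good. For a patient whose seated readings are all worse than T0, the recorded value is only the least uneven seated reading. Such patients enter a primary outcome and two secondary outcomes with values that look the same as those of patients who improved. The Background section names personalized mobilization plans as the purpose of the duration results, so the meaning of this variable matters.

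**Working it through.** **The plan's own figure.** The document states no figure for this rule. Its only sample-size figure, "a two-sided significance level (α) of 0.05 and a target power of 80% would require 10 subjects (19", comes without an effect size or SD and has no bearing here.

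**The rule as a formula.** Let HI(t) be the ventral-to-dorsal ratio and D(t) = |HI(t) − 1|. The rule returns the t in {15, 30, 60, 90, 120} min with the smallest D(t). D(T0) does not appear.

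**Two constructed records** (illustrative values, not trial data):

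| Record | D(T0) | D at 15, 30, 60, 90, 120 min | Rule returns |
|---|---|---|---|
| A: T0 1.10; then 1.45, 1.40, 1.35, 1.30, 1.25 | 0.10 | 0.45, 0.40, 0.35, 0.30, 0.25 | 120 min |
| B: T0 1.05; then 0.80, 0.75, 0.70, 0.72, 0.70 | 0.05 | 0.20, 0.25, 0.30, 0.28, 0.30 | 15 min |

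In A the best seated distance is 0.25 against 0.10 in bed. In B it is 0.20 against 0.05. Both patients were more homogeneous in bed throughout, and both receive a duration.

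**How often, without a distributional model.** Suppose sitting has no effect and the six readings are exchangeable without ties. Each is then equally likely to be the closest to 1, so P(T0 closest) = 1/6 = 16.7%, and 50 × 1/6 = 8.3 patients. The average duration assigned is (15 + 30 + 60 + 90 + 120)/5 = 63 min, which is a random pick among the five times.

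**How often, under assumptions.** None of the following inputs is in the document. Each scenario has 400,000 simulated patients and a common level for the five seated readings. The share is that of patients whose seated readings are all further from 1 than T0.

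Log-normal index, T0 median 1.5, log-scale SD 0.3 between patients and 0.1 between readings:

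| Mean log shift on sitting | Response SD 0 | 0.15 | 0.30 |
|---|---|---|---|
| 0 | 0.166 | 0.283 | 0.396 |
| −0.1 (about 10% fall) | 0.078 | 0.178 | 0.319 |
| −0.2 (about 18% fall) | 0.096 | 0.142 | 0.267 |

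Normal index, between-patient SD 0.3, within-patient SD 0.05 to 0.3:

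| Mean in bed → seated | Share |
|---|---|
| 1.5 → 1.5 | 0.166 to 0.167 |
| 1.5 → 1.4 | 0.047 to 0.123 |
| 1.5 → 1.3 | 0.058 to 0.098 |
| 1.3 → 1.5 | 0.283 to 0.882 |

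**Does this bias the secondary outcomes?** In the log-normal scenarios the mean assigned duration is 62.8 to 63.3 min in patients without improvement and 62.9 to 63.1 min in the others, so removing the former changes nothing on average. No scenario has seated times that truly differ, so the simulation neither shows a distortion nor rules one out.

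**How well would T0 screen patients?** The comparison sets the best of five readings against a single one. With no effect, 1 − 1/6 = 5/6 = 83% would still pass as improved. In the other log-normal scenarios, 32% to 65% of patients whose noise-free index is not closer to 1 when seated would pass. Median T0 is 0.96 to 1.39 in the patients excluded and 1.54 to 1.59 in those kept, so the screen selects on T0.

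**The case against.** The strongest reply is that the two primary outcomes answer different questions: whether homogeneity improves, and which seated time is best. Finding no improvement and finding 120 min the least uneven seated time are compatible. This stands. A reader might infer that the two outcomes contradict each other, or that the trial would hide a lack of benefit. The documents do not support either inference: improvement is itself primary, T0 is recorded for every patient, and the before/after comparison is planned at each time point. None of that, however, changes the duration assigned to a patient.

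A reader might also infer that the comparison by surgical method and the bed-rest correlation are distorted. That is not demonstrated, as shown above. Nor does the document say that a duration will be recommended to individual patients. Participation ends at 120 min, and the Background describes the duration results as exploratory groundwork for later plans.

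Two objections carry less weight. First, T0 is not expressly excluded and could be read as time 0, so that records A and B would score 0 min. This fits poorly with a baseline taken before seating, and if it was meant it has to be written, since two analysts could otherwise score record A as 0 or 120 min. Second, the handling of patients without improvement might be left to an analysis plan that is not shown. But Definitions already fixes a complete rule for a primary outcome, and the objection is to what that rule returns.

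The rule might instead be meant for the cohort as a whole. The planned correlation with bed rest time needs a value per patient, and the gap is the same at cohort level.

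**Conclusion.** The point holds as a flaw in the definition of a primary outcome. As written, on its ordinary reading, the rule assigns 15 to 120 min to every patient with seated readings, including those who were more homogeneous in bed at every comparison, and it would do the same for cohort means.

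The one size that needs no assumed variability is 1 in 6 patients, about 8 of 50, given no effect of sitting and exchangeable readings without ties. The simulated shares run from about 5% to 40% when sitting helps or is neutral on average, and from 28% to 88% when it worsens the index. They rest entirely on assumed means and SDs and serve only to show that the share is not fixed by the design.

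The study can go ahead, but the definition should be amended before analysis. The conclusion does not extend to biased secondary outcomes.

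**What to change.** 1. Amend Definitions so that T0 is the comparator. Where no seated index is closer to 1 than the patient's own T0 index, record *no improvement over T0 observed*.
2. At cohort level, name an optimal time only if the mixed-model contrast of that time with T0, in distance from 1, favours it. Statistical Analysis already provides for mixed models.
3. Report the number of patients without improvement descriptively. State beside it that the best of five readings against one T0 reading would class about 5 in 6 patients as improved with no true effect, so the count is not a responder rate.
4. Keep the comparison by surgical method and the bed-rest correlation in all patients, using the seated time closest to 1. Exclude the patients without improvement only as a sensitivity analysis, because that exclusion selects on T0.

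The cost is small: a short change to the definition, one extra category and one sensitivity analysis. T0 is already collected, so no new measurement is needed.
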